##### Spurious Data

Data quality (eg, consistency and accuracy) will be assessed at the point of data extraction through an outlier analysis comparing the covariate’s values to plausible biological measures. Spurious values will be categorized as missing values and handled according to the methodology layout.

### Ethical Considerations

Anonymized electronic health record data were accessible for research purposes following ethical approval from the Central University Research Ethics Committee at the University of Oxford (under reference R80951/RE001) for human participant research. Anonymized patient data were retrieved from electronic health record providers from those users who had consented for their data to be used for secondary research purposes. No form of compensation was provided to participants. Generative artificial intelligence was not used in any portion of the manuscript.

## Results

The primary care cohort comprised 1704 practices and 7,396,702 registered patients between the January 1, 2012, and December 31, 2022 (Figure 1). We have created an initial clinical code ontology using existing SNOMED CT–curated variables for our sociodemographic variables, hepatitis, and CLD by etiology (Multimedia Appendix 1). The ontology will be expanded to include paraclinical indicators of CLD to identify cases where an explicit diagnosis or specific etiology has not been recorded. Other relevant covariates will be created as required for the study.

The phases of this study will include curating the required variables, conducting our data extraction, statistical analysis, and reporting of the findings through scientific publications.

## Discussion

### Overview

This study will inform on the state of preventive Hep A vaccination for people with CLD in a representative primary care sentinel network in England. From a total of 7.4 million patients in the RSC network, we will report on the sociodemographic and clinical characteristics of people with CLD with and without Hep A vaccination, for 1 and 2 doses.

The multistate model, adjusted for study risk factors, will identify those associated with having the vaccination. This will inform on the individual characteristics that are associated with an immunization, informing on the subgroups that could benefit from higher engagement with preventive primary care. Any disparities identified could be used to target clinical and public health interventions to improve vaccination coverage in this at-risk group.

### Comparisons With Previous Work

The results will be compared to previous reports on preexposure Hep A vaccination coverage rates of 10%-50% in the United States [2,9,10,12]. For the United Kingdom, there are no published reports on vaccination coverage in this subpopulation, to the best of our knowledge.

### Limitations

Selection and misclassification biases can be associated with the retrospective study design. However, this can be mitigated by the availability of reliable records in the database. Similarly, the retrospective study design has a limitation to establishing causal relationships due to the temporality and lack of randomization. However, retrospective associations can be a timely source of epidemiological data to guide further research.

There exists potential confounding due to case-mix characteristics, which will be mitigated through multivariate time-to-event modeling in the multistate model.

Large general practice databases are susceptible to coding errors or inaccuracies that may be associated with ascertainment and misclassification biases. This is mitigated by the large representative sample of UK practices within the RSC network, which controls for random error and variation on these parameters [18].

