### Setting

#### Data Source

Data will be extracted from the PCSC of the RSC. The PCSC consists of a nationally representative sample of 7.4 million patients registered in primary care practices in England [17,18]. Pseudonymized data will be extracted from the secure environment of the Oxford-RCGP Clinical Informatics Digital Hub (ORCHID) [19].

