### Variables

#### Overview

The study population is those with CLD as an index condition, as defined in the inclusion criteria. The variables will be curated for the identification of CLD-related codes in the computerized medical records of adults registered in the RSC network (Multimedia Appendix 1).

Comparisons will be conducted between population subgroups with different CLD etiologies, sociodemographic characteristics, complications, and comorbidity profiles.

The outcome of the first objective will be the coverage rates of Hep A vaccination among those with CLD.

For the second objective, we will explore significant independent predictors of the following outcomes among those with CLD: (1) one dose of Hep A vaccination and (2) two doses of Hep A vaccination.

Hep A vaccination, as defined by the UK vaccination scheme, includes an initial 0.5 mL for 1 dose, followed by a booster dose of 0.5 mL after 6-12 months. The booster dose may be delayed by up to 3 years if not given after the recommended interval following the primary dose [8]. For this study, we will report boosters administered within 12 months of the first dose for the base case analysis and 3 years from the first dose for a sensitivity analysis. Hep A vaccination in the United Kingdom is available as a monovalent vaccine, as a combined Hep A and hepatitis B vaccine, and as a Hep A and typhoid vaccine [7]. We will consider any Hep A vaccination type as an outcome.

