### Statistical Analysis

#### Reporting Hep A Vaccination Coverage in People With CLD

Hep A vaccination rates will be calculated using the number of vaccinated people with CLD as the numerator and estimates of the CLD population in the ORCHID data set as the denominator. Baseline characteristics of each study group (eg, age and gender) will be summarized using descriptive statistics, including measures of dispersion (eg, SDs and IQRs).

To compare individual characteristics by vaccination status (eg, CLD disease type, sociodemographic characteristics, complications, and comorbidities), we will use descriptive statistics, with pairwise comparisons using the chi-square or Fisher exact tests for categorical variables and the *t* test or Wilcoxon test for continuous variables. If stratification involves more than 2 groups, differences across groups will be tested using the Kruskal-Wallis test for continuous variables and the Pearson chi-square test for categorical variables, followed by pairwise comparisons as above described. All statistical tests will be 2-sided with *P*<.05 considered statistically significant.

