### Conclusions

This descriptive epidemiological study will fill an important gap in our knowledge about Hep A vaccination in people with CLD in the United Kingdom by describing the uptake of Hep A vaccine in people with CLD and reporting any disparities or differences in characteristics of the vaccinated population.

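### The Limitations section credits a large sample with mitigating misclassification bias, but sample size reduces only random error, so coverage and disparities should be stated as recorded in primary care

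*Protocol article*

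**What the plan says.** All on this point is in the protocol article.

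- **Limitations.** Large general practice databases are described as "susceptible to coding errors or inaccuracies that may be associated with ascertainment and misclassification biases". The next sentence says this is "mitigated by the large representative sample of UK practices within the RSC network, which controls for random error". Earlier in the section, selection and misclassification biases from the retrospective design are answered with "this can be mitigated by the availability of reliable records in the database". No figure for completeness of vaccine recording is given.
- **Data Source.** The data come from a "nationally representative sample of 7.4 million patients registered in primary care practices in England". No other source of vaccination data is named.
- **Reporting Hep A Vaccination Coverage in People With CLD.** Coverage is to be derived "using the number of vaccinated people with CLD as the numerator and estimates of the CLD population in the ORCHID data set as the denominator".
- **Variables, Overview.** "We will consider any Hep A vaccination type as an outcome". In context this concerns the product (monovalent or combined), not where the dose was given.
- **Conclusions.** The study is to fill a gap by "describing the uptake of Hep A vaccine in people with CLD and reporting any disparities", with no statement that uptake means recorded uptake. The Discussion overview adds that any disparities found could be used to target clinical and public health interventions.

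**The concern.** The sentence names a systematic error and offers a remedy for random error. A reader who accepts it will treat the narrow intervals of a very large database as evidence that coverage is close to the truth, and any significant group difference as a real difference in vaccination.

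No other planned step deals with an unrecorded dose. The Missing Data rules act on values known to be missing, whereas an absent vaccine code looks the same as no vaccination. The Spurious Data check is an outlier check on covariates. The Sensitivity Analysis varies the dose 2 window and allows an optional complete-case analysis. The Data Quality section cites surveillance experience.

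Coverage and disparities are the study's main outputs, so the error bears on what the study may conclude.

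**Working it through.** **Inputs from the protocol article.** Expected coverage 10% to 50%, and 1656 patients with CLD per year (Study Size); two-sided P<.05 (Statistical Analysis).

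**Assumed, because the documents give no figure.** Recording sensitivity Se, the share of truly vaccinated people whose vaccination is in the practice record: range 0.60 to 0.95. False-positive vaccine records: none.

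**Step 1. The plan's own figure.** 20.7/100,000 × 7.4 million = 1531.8, not 1656. The stated figure follows from 8 million: 20.7/100,000 × 8 million = 1656. Then 10% and 50% of 1656 give 165.6 and 828, as stated. That mismatch is a separate matter. Here 1656 serves only as an example of n, and the result does not depend on it.

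**Step 2. Size of the bias.** Observed coverage = p × Se, so bias = −p(1 − Se). There is no n in this expression.

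| True p | Se 0.95 | Se 0.90 | Se 0.80 | Se 0.60 |
|---|---|---|---|---|
| 50% | 47.5% | 45% | 40% | 30% |
| 10% | 9.5% | 9% | 8% | 6% |

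**Step 3. What sample size does change.** Half-width = 1.96 × √[0.40 × 0.60 / n] for p = 50% and Se = 0.80:

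- n = 1656: 2.36 points
- n = 16,560: 0.75 points
- n = 165,600: 0.24 points

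The bias is −10 points in every row.

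**Step 4. Equal completeness in two groups.** Observed ratio = (p₁ × Se)/(p₂ × Se) = p₁/p₂. Coverage is too low, but the ratio of coverages is preserved. Absolute differences shrink by the factor Se.

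**Step 5. Unequal completeness, same true coverage of 30% (assumed).**

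| Se, group A vs B | Observed | Ratio | Odds ratio |
|---|---|---|---|
| 0.90 vs 0.80 | 27% vs 24% | 0.89 | (0.24/0.76)/(0.27/0.73) = 0.85 |
| 0.90 vs 0.70 | 27% vs 21% | 0.78 | (0.21/0.79)/(0.27/0.73) = 0.72 |
| 0.90 vs 0.60 | 27% vs 18% | 0.67 | (0.18/0.82)/(0.27/0.73) = 0.59 |

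For 0.90 vs 0.70, the probability that this spurious difference reaches P<.05 (normal approximation, two proportions) is 0.80 with 800 per group and about 1.00 with 8000 per group. A larger sample makes the false finding more likely.

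**Step 6. Masking.** In general, observed ratio = true ratio × (Se₁/Se₂). A true ratio of 0.778 with Se 0.90 in the numerator group and 0.70 in the other is observed as 0.778 × 0.90/0.70 = 1.00, so a real disparity disappears.

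**The case against.** The best defence has five parts.

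1. **The bias is disclosed, and the sentence can be read narrowly.** A large sample does average out coding variation between practices. That is fair for error that is as often positive as negative. A missed dose is not of that kind: it can only move a person from vaccinated to unvaccinated, so even misses scattered at random across practices do not cancel. Representativeness helps generalisation to England; it does not help measurement. The sentence cites a source that is not available here. Even a good completeness figure in it would be a different argument from sample size.

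2. **The scope is already primary care.** The abstract, introduction and aims do say so. They name the setting, not the fact that the outcome is what the practice record contains. The Objectives and Conclusions drop even the setting.

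3. **The documents say nothing about doses given elsewhere.** This stands. A reader might infer that doses from hospital, travel or other services go unrecorded, and unequally by etiology or social group. The documents contain no evidence for that. A dose copied into the practice record causes no bias, and under equal completeness the coverage ratios hold. Unequal bias is a possibility, not a finding.

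4. **Vaccine code handling belongs in the full protocol or code list.** This also stands. The only appendix listed concerns codes for CLD, and no vaccine code list is shown. It cannot be said that codes for outside doses or for dose number are ignored, or that a true second dose would be counted as a first.

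5. **The completeness gaps are chosen, and the second objective uses an adjusted multistate model.** True. The odds ratios above are crude illustrations, not predictions. Adjustment for covariates does not correct an outcome recorded with different completeness across levels of those same covariates.

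**Conclusion.** The concern holds in a limited form. The mitigation sentence claims a property that the design does not have: no sample size reduces systematic misclassification of vaccination.

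- **Firm.** Any vaccinated person missing from the practice record lowers estimated coverage, by p(1 − Se), whatever n is.
- **Dependent on assumptions.** The size. For Se from 0.95 down to 0.60, the loss runs from 2.5 to 20 points at true coverage of 50%, and from 0.5 to 4 points at 10%. False-positive vaccine records are taken as nil.
- **Conditional.** If completeness differs between groups, disparities could be created or masked.
- **Not claimed.** That the net bias in coverage is downward. Errors in coding CLD affect who is in the denominator and could move coverage in either direction.

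The planned cohort and model can stand. What needs to change is the interpretation, and the change is cheap.

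**What to change.** 1. **Replace the mitigation sentence** in Limitations. Possible wording: *A large sample reduces random error but not ascertainment or misclassification bias. Vaccinations absent from the practice record are counted as non-vaccination and would lower estimated coverage. If completeness of recording differs between groups, comparisons could be distorted in either direction. Errors in coding CLD could raise or lower coverage.* Support the remark about reliable records with a figure for vaccine recording, or remove it.

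2. **Describe the outcome as Hep A vaccination recorded in primary care** in Objectives, Variables and Conclusions, and describe disparities in the same terms.

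3. **Add a simple quantitative bias analysis.** Show how coverage and the main group contrasts change over a stated, assumed range of recording sensitivity (for example 0.60 to 0.95), once with equal and once with unequal values between groups. Report it as context. It should not be a pass/fail rule for calling a difference a disparity: letting completeness differ freely over that range would dismiss every coverage ratio between 0.60/0.95 = 0.63 and 0.95/0.60 = 1.58, on limits that are themselves assumed.

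**Cost.** Some rewording and a short calculation, with no new data source. The price is a more cautious conclusion.

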### Conclusions

This descriptive epidemiological study will fill an important gap in our knowledge about Hep A vaccination in people with CLD in the United Kingdom by describing the uptake of Hep A vaccine in people with CLD and reporting any disparities or differences in characteristics of the vaccinated population.

### Data Handling and Record Keeping

Data are held on dedicated, secure servers at the RCGP data and analytics hub in the Clinical Informatics and Health Outcomes Research Group, based at the Nuffield Department of Primary Care Health Sciences, University of Oxford. The research group’s secure network is sited behind a firewall within the university’s network; all inbound connections are blocked, but outbound connections are allowed. Only staff members or associated members of the research group approved by the head of department can access the data from a virtual desktop (on the ORCHID secure server) using a University of Oxford computer and their unique access credentials. The use of personal equipment is not permitted and cannot be connected to a secure network. Pseudonymized study data will be archived for at least 5 years.

## Appendix

Multimedia Appendix 1 Preliminary list of SNOMED CT codes used to identify individuals with chronic liver disease registered in the RSC network in England between the 1st January 2012 and the 31st December 2022.

## Abbreviations

ALD: alcohol-related liver disease
CH-B: Chronic hepatitis B
CH-C: Chronic hepatitis C
CLD: chronic liver disease
CMMS: Cambridge Multimorbidity Score
CONSORT: Consolidated Standards of Reporting Trials
HAV: hepatitis A virus
Hep A: hepatitis A
NAFLD: nonalcoholic fatty liver disease
ORCHID: Oxford-RCGP Clinical Informatics Digital Hub
PCSC: Primary Care Sentinel Cohort
RCGP: Royal College of General Practitioners
RSC: Research and Surveillance Centre
SNOMED CT: Systematized Nomenclature of Medicine Clinical Terms
